### **3.10 Data collection methods and management**

All data including demographic data, medical history, medical record, laboratory data, 2D echocardiography, AE, and SAE will be recorded at CRF. The investigators will maintain individual records (ICF and CRF) for each patient as source data. A copy of each CRF will be sent to KCGMH-CTC for data management.

### **3.11 Statistical methods**

All baseline characteristics will be used to investigate comparability of both trial arms. The primary outcome evaluation (CAL rate at 6-8 weeks) and secondary outcome of Z score of coronary arteries and CAL rate at 6 months will be performed on per-

protocol (PP) population while the other secondary outcome will be performed on intention-to-treat (ITT) population. Continuous variables will be described by using the mean (standard deviation) or median (interquartile range) as appropriate, categorical variables by using count (percentage). The participant characteristics will be compared using a  $\chi^2$  test for categorical variables, and a t test or Wilcoxon rank sum test for continuous variables. P values < 0.05 will be considered statistically significant.

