### **3.8 Allocation**

Eligible participants will be randomized to either the IVIG alone or IVIG plus high-dose aspirin on an equal ratio. The investigator or his/her delegate will contact the Clinical Trial Center of Kaohsiung Chang Gung Memorial Hospital (KCGMH- CTC) after confirming that the patient fulfills all the inclusion/exclusion criteria. The KCGMH- CTC will assign a treatment arm to the patient. Randomization will use permuted blocks of random sizes. The block size will not be disclosed to ensure concealment.

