### **Appendix B: Case Report Form**

### **Appendix C: Common Terminology Criteria for Adverse Events (CTCAE) version**

**4.03. (A complete copy of the CTCAE version 4.03 will be held in each site study file)**

## **Statistical analysis**

All of the baseline characteristics are used to study the comparability of both trial arms. The primary outcome evaluation and safety evaluation are carried out on the intention-to-treat (ITT) population. Continuous variables will be described using either the mean (standard deviation) or median (interquartile range), as appropriate, and categorical variables will use count (percentage). Participants' characteristics are compared using a  $\chi^2$  test for categorical variables and a t-test or Wilcoxon rank sum test for continuous variables.  $P$ -values < 0.05 are considered statistically significant.

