**Demographic Data**

**Gender:** ☐ Male ☐ Female, **Birthday:** □□□□/□□/□□ (yyyy/mm/dd)

**Body weight:** □□.□ Kg, **Body height:** □□□.□ cm, **Body temperature:** □□.□ °C

**Baseline laboratory data date:** 20□□/□□/□□ (yyyy/mm/dd)

| Item | Value | Unit       | Item       | Value | Unit    | Item       | Value | Unit |
|------|-------|------------|------------|-------|---------|------------|-------|------|
| WBC  |       | 1000/ul    | MCHC       |       | gHb/dl  | Monocyte   |       | %    |
| RBC  |       | Million/ul | RDW-SD     |       | %       | Eosinophil |       | %    |
| HGB  |       | g/dl       | RDW-CV     |       | %       | Basophil   |       | %    |
| HCT  |       | %          | PLT        |       | 1000/ul | AST/GOT    |       | U/L  |
| MCV  |       | fL         | Segment    |       | %       | ALT/GPT    |       | U/L  |
| MCH  |       | pg/cell    | Lymphocyte |       | %       | CRP        |       | mg/L |

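### Comparability of the arms is assessed by baseline significance tests, which cannot show whether an imbalance matters for CAL, and no baseline covariate is pre-specified for the primary comparison

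*Combined protocol and SAP*

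**What the plan says.** Section 3.11 opens with "All baseline characteristics will be used to investigate comparability of both trial arms". It then assigns a chi-square "test for categorical variables, and a t test or Wilcoxon rank sum test for continuous variables", and closes with "P values < 0.05 will be considered statistically significant". The Statistical analysis section after the appendix list does the same: "All of the baseline characteristics are used to study the comparability of both trial arms", with the same family of tests and the same threshold. No other criterion of comparability appears.

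Section 3.8 says "Randomization will use permuted blocks of random sizes" and names no stratification factor. Neither statistical section names a baseline covariate or an adjusted model. Nor does either name a test or confidence interval for the primary non-inferiority comparison; the listed tests are attached to participant characteristics.

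The two sections also differ on the primary population. Section 3.11 has a sentence beginning "The primary outcome evaluation (CAL rate at 6-8 weeks) and secondary outcome of Z score of coronary arteries and CAL rate at 6 months will", which assigns these outcomes to the per-protocol set. The Statistical analysis section assigns the primary outcome to the ITT set. Section 3.9 makes the trial open-label.

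**The concern.** Among all randomised children, any baseline difference arises by chance, so the null hypothesis of a baseline test is true by design. What matters is how far an imbalance moves the CAL difference. That depends on its size and on how strongly the factor predicts CAL, and the P value ignores the second.

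With no stratification and no named covariate, nothing in the plan limits how far the estimate moves with chance imbalance. A plan that tests many characteristics and is silent on what follows also leaves room to choose covariates after the data are seen. That matters more if the primary set is per-protocol: children are then removed after open-label allocation, and the arms compared are no longer exactly those that were randomised.

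**Working it through.** **Inputs.** Section 3.6 gives CAL-free rates of 0.846 (test) and 0.83 (standard), a margin of −0.10, α = 0.05, β = 0.2, 125 evaluable per group, and 139 per group after 10% dropout. My count of baseline items on the CRF is 24: sex, age, weight, height, temperature, days of fever from the recorded fever start, and the 18 laboratory values under "Baseline laboratory data date". The documents give no association between any baseline factor and CAL, so factor strengths below are assumptions.

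**1. The plan's own figure.** The variance sum is 0.846 × 0.154 + 0.83 × 0.17 = 0.2714. Then n = (1.645 + 0.842)² × 0.2714 / 0.116² = 124.7, so 125 per group; 125 / 0.9 = 138.9, so 139. This reproduces the plan, and shows that α is one-sided 0.05 (one-sided 0.025 would need 159). The standard error at 125 per group is √(0.2714 / 125) = 0.0466, and power is Φ(0.116 / 0.0466 − 1.645) = 80%.

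**2. False flags under correct randomisation.** For k independent tests, P(at least one P < 0.05) = 1 − 0.95^k.
- k = 24: 71%, with 1.2 flags expected.
- 24 items with related items correlated in blocks (assumed r of 0.7 to 0.95, simulated): 60–63%.
- All 24 items correlated at 0.5 (simulated): 46%.
- k = 13, independent: 49%.

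**3. The same P value can mean very different things for CAL.** At 125 per arm the largest unflagged imbalance in a binary factor of prevalence p is 1.96 × √(2p(1 − p) / 125): 9.9 points at p = 20% and 11.4 points at p = 30%. The shift in the CAL difference is that imbalance times the risk difference between the factor's levels. Three assumed factors, each giving 17% CAL overall:

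| Assumed factor | Prevalence | CAL by level | Risk difference | Largest unflagged shift |
|---|---|---|---|---|
| Strong | 20% | 45% vs 10% | 35 points | 0.099 × 35 = 3.5 points |
| Moderate | 30% | 35% vs 9.3% | 25.7 points | 0.114 × 25.7 = 2.9 points |
| Weak | 20% | 30% vs 13.75% | 16.25 points | 0.099 × 16.25 = 1.6 points |

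For a factor unrelated to CAL the shift is nil at the same P value. For scale, the lowest estimate that passes is −0.10 + 1.645 × 0.0466 = −2.3 points, which is 3.9 points below the planned +1.6.

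**4. What adjustment gains.** A binary factor explains R² = p(1 − p)d² / (0.17 × 0.83) of the outcome variance, where d is its risk difference. The adjusted standard error is about 0.0466 × √(1 − R²).
- Strong: R² = 0.0196 / 0.1411 = 13.9%, SE 0.0432, power 85%.
- Moderate: R² = 0.0139 / 0.1411 = 9.8%, SE 0.0442, power 84%.
- Weak: R² = 0.0042 / 0.1411 = 3.0%, SE 0.0459, power 81%.

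Simulation with a covariate-standardised risk difference agrees: about 80% unadjusted, 81–86% adjusted.

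**5. Type I error.** With the true excess exactly at the margin, and one assumed factor of prevalence 20–50% and risk difference 20–40 points, the simulated one-sided error is 5.0–5.2% unadjusted and 5.1–5.4% adjusted.

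**The case against.** The strongest reply is that baseline P values are a reporting habit with no stated consequence. Neither section says that a significant test makes the arms unbalanced, or that a non-significant one makes them comparable, and the P < 0.05 sentence is general. The unadjusted comparison is valid, and the absence of a covariate is silence within a larger silence, since no primary method is named at all. The suggested covariates also have no prognostic support in the documents. All of this stands, and it limits the point to efficiency and pre-specification.

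Three stronger readings are tempting, and the documents do not support them.

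- *The tests miss most imbalances that could change the result.* A reader might support this by calculating the tests' power against arms that truly differ. But in a randomised trial the imbalance is the observed difference, and its P value is then fixed. At 139 per arm an observed 20% vs 30% gives z = 1.93, P = 0.054, and is never flagged; an observed 0.25 SD gives t = 0.25 × √(139 / 2) = 2.08, P = 0.038, and is always flagged. The share unflagged also depends on prognostic strength: across assumed factors in simulation it is 7–87% for shifts above 2 points and 0–75% for shifts above 3 points.
- *The tests declare most correct randomisations unbalanced.* The plan fixes no number of tests and attaches no declaration to one small P value, and the proportion falls below half under strong overall correlation.
- *False non-inferiority is inflated.* For the three factors above, with the true excess at the margin, the unadjusted error is roughly 8–11% when a non-significant imbalance of at least 5 points favours the test arm. That happens in only 13–16% of trials. The mirror-image trials have roughly 1–3%, and all trials with a non-significant baseline test average about 5%.

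**Conclusion.** The point holds as a matter of efficiency and pre-specification. Baseline significance testing is the only stated comparability method, and it does not answer whether an imbalance matters for CAL. No covariate or stratification factor is named. The overall false non-inferiority rate is about 5% either way, so the trial's validity is not in question on this ground.

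The gain from adjustment is 1 to 6 points of power at the planned rates (about 80% to 81–86%). It rests on one factor with an assumed CAL risk difference of about 16 to 35 points, 125 evaluable per arm and a one-sided 5% test. It would be near zero for a factor that hardly predicts CAL. Fixing the covariates in advance also removes a post-hoc choice, which carries more weight if the per-protocol analysis is primary.

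**What to change.** In section 3.11 and the Statistical analysis section:

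1. Present baseline data descriptively, without P values.
2. State that the primary risk difference in CAL-free rate at 6–8 weeks, and its confidence bound against −0.10, are estimated with adjustment, either by standardisation from a logistic model or as a stratified risk difference. State the sidedness of the bound.
3. Fix a short covariate list before data are seen and keep it whatever imbalance is observed. Candidates already collected are age, sex, baseline CRP, and days of fever at treatment. The last needs the fever start from the Screen Visit form and the IVIG start from the Treatment Visit form. The investigators should confirm the choice, since the documents give no prognostic evidence. The list must stay short: the planned rates imply only 0.17 × 125 + 0.154 × 125 ≈ 40 CAL events.
4. Report the unadjusted difference alongside.

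Baseline coronary Z score could be added only after a reconciliation. Section 3.4 plans it, but the timeline in section 3.5 marks no baseline echocardiogram and the screening CRF has no field for one.

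The cost is plan wording, a few lines of code and a simple rule for missing baseline values. The downside is little gain if the chosen factors prove weakly prognostic.

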### 3.4 Outcomes

#### Primary outcome

- **CAL**

The primary outcome is CAL at 6-8 weeks.

CAL will be evaluated by experienced pediatric cardiologists (at least 2 years experience of pediatric 2D echocardiography) using 2D echocardiography. The luminal diameter of left main coronary artery (LMCA) is measured at a point between the ostium and the first bifurcation of the artery (as Figure below). The luminal diameter of left anterior descending artery (LAD) is measured distal to and away from the bifurcation of the branch from the LCA. The luminal diameter of right coronary artery (RCA) is measured in the relatively straight section of the artery just after rightward turn from the initial anterior course of the artery. Definition of CAL is coronary artery luminal diameter greater than  $+3SD$  in one of the three proximal segments or greater than  $+2.5SD$  in two of the three proximal segments. The calculation of Z score is based on the website of Taiwan Society of Pediatric Cardiology ([http://www.tspc.org.tw/service/z\\_score.asp](http://www.tspc.org.tw/service/z_score.asp)).

[figure not shown]

**Figure:** coronary artery luminal diameter measurement in 2D echocardiogram

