#### Secondary outcomes

- **IVIG resistance rate:**

IVIG resistance is defined as persistent or recrudescent fever at least 48 hours but not longer than 7 days after completion of the first IVIG treatment.

- **Duration of fever after IVIG treatment**

We will record the body temperature every 6 hour during the hospitalization period.

- **Duration of hospitalization**

We will record the hospitalization duration from admission (or arriving emergency room) to discharge date.

- **Laboratory data**

Laboratory data of CBC/DC, GOT/GPT, and CRP will be checked at baseline, day 5, and 6-8 week.

- **Z score of coronary arteries**

We will estimate Z score of the proximal segments of LMCA, LAD, and RCA at baseline, Day 5, 6-8 weeks, and 6 month with 2D echocardiography. The calculation of Z score is based on the website of Taiwan Society of Pediatric Cardiology ([http://www.tspc.org.tw/service/z\\_score.asp](http://www.tspc.org.tw/service/z_score.asp)).

- **CAL rate at 6 months**

- **Adverse event (AE) and serious adverse event (SAE)**

We will record AE and SAE. Severity of AE will be based on Common Terminology Criteria for Adverse Events (CTCAE) version 4.03.

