### 3.6 Sample size

The sample size determination is based on the result of our retrospective data.[16] The estimated proportions of CAL are 17% after IVIG and high-dose aspirin combination treatment and 15.4% after IVIG alone treatment. We consider the difference less than 10% is of no clinical importance. The following contents are the statistical basis for estimating sample size for this trial.

$$H_0: P_T - P_S \leq \delta$$

$$H_A: P_T - P_S > \delta$$

$$P_T: \text{CAL-free rate in test group} = 0.846$$

$$P_S: \text{CAL-free rate in standard group} = 0.83$$

$$\delta = -0.1$$

Assume that the type I and type II error rates are  $\alpha = 0.05$ ,  $\beta = 0.2$ , respectively. The clinically meaningful difference  $\delta$  is -0.1. The CAL-free rate of test group (IVIG alone)  $P_T$  is 0.846 and that of standard group (IVIG + high dose aspirin)  $P_S$  is 0.83.

Assume the sample sizes of two groups are equal, the sample size of each group for the non-inferiority trial is 125 patients. Offsetting a maximal dropout of 10%, 139 patients are required for per group. That is, a total sample size of 278 patients is required for the trial.

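### The primary CAL comparison has no named estimator and no covariate, although section 3.4 lists a baseline coronary Z score that the schedule and CRF do not capture; collecting it and adjusting for it would be a cheap gain in precision

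*Combined protocol and SAP*

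**What the plan says.** **Endpoint.** Section 3.4 (Primary outcome) makes CAL at 6-8 weeks a threshold on coronary size: "Definition of CAL is coronary artery luminal diameter greater than" +3SD in one of three proximal segments, or +2.5SD in two of them. Section 3.4 (Secondary outcomes) adds: "We will estimate Z score of the proximal segments of LMCA, LAD, and RCA at baseline, Day 5, 6-8 weeks, and 6 month".

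**Primary analysis.** Section 3.11 introduces it with "The primary outcome evaluation (CAL rate at 6-8 weeks" and places it on the PP population. The SAP (Statistical analysis) states: "The primary outcome evaluation and safety evaluation are carried out on the intention-to-treat (ITT) population". Neither gives a test, confidence interval, margin comparison or covariate for the primary endpoint. The chi-square, t and Wilcoxon tests in both places are attached to participant characteristics.

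**Sample size.** Section 3.6 compares two unadjusted proportions: "The estimated proportions of CAL are 17% after IVIG and high-dose aspirin combination treatment and 15.4% after IVIG alone treatment". On the margin it says: "We consider the difference less than 10% is of no clinical importance".

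**When echocardiography happens.** The section 3.5 schedule marks it at Day 5, 6-8 weeks and 6 months only; the enrolment, randomization and intervention cells are empty. The CRF pages for screening, randomization and treatment have no field for coronary diameter or Z score. The first such field is on the Day 5 page (Day 3 to 7), after treatment on Day 1.

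**The concern.** The baseline version of the outcome is the natural covariate here. CAL at entry is not an exclusion in section 3.2, and section 3.8 describes permuted blocks without stratification by coronary status. Neither design nor analysis therefore takes out the variation in 6-8 week CAL that was already present at entry. That variation stays in the standard error of the risk difference, in a trial planned at 80% power with a 1.6-point advantage assumed for the test arm.

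Prespecification also matters. Section 3.11 uses baseline characteristics only to examine comparability and says nothing about what follows if coronary size is unbalanced. In an open-label trial, a decision to adjust taken after seeing the data would be hard to defend.

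The adjustment needs a coronary measurement taken before treatment. Section 3.4 lists one; the schedule and CRF do not provide for it.

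**Working it through.** **Inputs.** From section 3.6: CAL-free rates 0.846 (test) and 0.83 (standard), delta -0.1, alpha 0.05, beta 0.2, 1:1 allocation, 10% dropout. The sidedness of alpha is not stated. One-sided 0.05 reproduces the plan's figure; one-sided 0.025 would give 159 per group. The share of outcome variance explained by baseline Z (R2) is not in the documents and is assumed.

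**1. Reproduce the plan's figure.**
- Variance sum: 0.846 × 0.154 + 0.83 × 0.17 = 0.1303 + 0.1411 = 0.2714.
- Distance from the margin: 0.10 + (0.846 - 0.83) = 0.116.
- n = 0.2714 × (1.645 + 0.842)² / 0.116² = 124.7, so 125 per group.
- 125 / 0.9 = 138.9, so 139 per group and 278 in total.

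Both agree with section 3.6. The calculation is an unadjusted difference in proportions.

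**2. Unadjusted power at 125 per group.** SE = sqrt(0.2714 / 125) = 0.0466. Power = Phi(0.116 / 0.0466 - 1.645) = 80.1%.

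**3. Effect of adjustment.** To a good approximation, adjustment multiplies the variance of the risk difference by (1 - R2). The half-width below is 1.645 × SE, in percentage points. The odds ratio is the approximate effect of one SD of a normally distributed baseline Z that yields that R2 at these CAL rates.

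| Assumed R2 | Odds ratio per SD | SE | Half-width | Power |
|---|---|---|---|---|
| 0 | 1 | 0.0466 | 7.7 | 80.1% |
| 0.02 | 1.5 | 0.0461 | 7.6 | 80.8% |
| 0.06 | 2 | 0.0452 | 7.4 | 82.2% |
| 0.14 | 3 | 0.0432 | 7.1 | 85.1% |
| 0.25 | between 4 and 6 | 0.0404 | 6.6 | 89.1% |

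An R2 of 0.14 is worth 125 / 0.86 = 145, about 20 extra children per group.

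**4. Check on the Z-score scale.** Correlation is lost when a Z score is cut into CAL yes or no, so a given correlation between baseline and 6-8 week Z scores buys less than the same correlation with CAL itself. Simulation used 1,500 trials per setting, bivariate normal Z scores cut at the planned CAL rates, and a standardised logistic model:

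| Correlation of underlying Z scores | Unadjusted power | Adjusted power |
|---|---|---|
| 0.3 | 80.3% | 82.4% |
| 0.5 | 81.4% | 85.7% |
| 0.6 | 79.9% | 87.1% |
| 0.7 | 80.2% | 89.2% |

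The gains are about 2, 4, 7 and 9 points.

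**5. Sensitivity to the assumed advantage.** If both arms are CAL-free at 0.83, SE = sqrt(2 × 0.1411 / 125) = 0.0475 and unadjusted power is Phi(0.10 / 0.0475 - 1.645) = 67.7%. An R2 of 0.14 brings it to 73.4%.

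**6. Is the covariate available?** Section 3.4 says yes; the section 3.5 schedule and the CRF say no. Section 3.10 says that echocardiography data are recorded on the CRF, so a baseline scan with no CRF field would not reach the analysis. The Day 5 value follows treatment, may be affected by it, and cannot stand in for baseline.

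**The case against.** The strongest reply is that this is an efficiency preference. An unadjusted risk difference is valid under randomisation, its standard error already allows for chance imbalance, and section 3.6 reaches its stated 80% power without covariates. All of that stands. Chance imbalance in coronary size is ordinary sampling variation and does not invalidate an unadjusted analysis.

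Four stronger readings are tempting, and the documents do not support them:

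- A reader might infer that the plan has chosen an unadjusted chi-square test for CAL. It has not: that test is tied to participant characteristics, and no primary method is named. The unadjusted reading comes from the sample-size formula alone. The missing estimator is the larger gap, and one edit can close both.
- A reader might infer from section 3.4 that a baseline Z score is in hand for each child, so that adjustment costs nothing. The schedule and CRF contradict this. On the CRF as written the value would be missing for all children and adjustment would gain nothing.
- A reader might take 9 points as the expected gain in power. That needs a correlation of 0.5 with the binary CAL outcome, or about 0.7 between the underlying Z scores. Nothing in the documents supports a covariate that strong; a weak one gives 1 to 2 points.
- A reader might suppose that randomisation protects the adjusted estimate from bias wherever it is applied. That protection belongs to the ITT set of the SAP. It does not carry over automatically to the PP set of section 3.11.

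These limit the size and cost of the point. They leave the recommendation in place.

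**Conclusion.** The point holds as a recommended improvement. The plan lists the baseline version of its own endpoint, does not provide for capturing it, and gives the primary comparison neither a covariate nor an estimator. Prespecified standardised adjustment would raise power at 125 per group from 80.1% to between 80.8% and 89.1% for an assumed R2 of 0.02 to 0.25. The gain is about 4 points if the underlying Z scores correlate at 0.5.

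This rests on the rates and margin in section 3.6, a one-sided alpha of 0.05, a truly pre-treatment baseline scan, and an R2 that the documents do not give. It is no reason to call the sample size wrong: 125 per group and 278 in total reproduce exactly and do not depend on adjustment.

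**What to change.** 1. **Reconcile the data collection.** Bring the section 3.5 schedule and the CRF into line with section 3.4 by marking the baseline echocardiogram and adding a dated CRF field for the pre-treatment LMCA, LAD and RCA diameters and Z scores. State that the Day 5 value is not to be used as baseline.
2. **Name the primary estimator in section 3.11 and the SAP.** Estimate the CAL-free risk difference (test minus standard) by g-computation from a logistic model with treatment and the baseline maximum Z over the three segments. Use a robust or bootstrap confidence interval at a stated level, compared with the 10-point margin. Standardising keeps the estimate on the scale of the margin, which an odds ratio would not. State how a child without a baseline Z is handled, for example with a missing-value indicator.
3. **Report the unadjusted risk difference and its interval** beside the adjusted one.
4. **Settle the population.** Make section 3.11 (PP) and the SAP (ITT) agree on the primary analysis set.

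**Cost.** A CRF field and a schedule entry, modest extra analysis, and reliance on a working model. If the baseline scan in section 3.4 is already being done, no procedure is added; if it is not, one echocardiogram per child is. No change to the sample size is needed.

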**Sample size estimation:**

A total of 278 patients will be recruited to achieve 250 per-protocol (PP) patients.

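### Coronary Z scores and 6-month CAL are analysed per protocol only; an as-randomised analysis should lead, with per protocol beside it

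*Combined protocol and SAP*

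**What the plan says.** Protocol section 3.11 (Statistical methods) sets the analysis populations in one sentence. After placing the primary outcome on PP, it treats the two coronary secondary outcomes the same way: "secondary outcome of Z score of coronary arteries and CAL rate at 6 months will be performed on per", running on to "protocol (PP) population while the other secondary outcome will be performed on intention-to-treat (ITT) population".

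Section 3.4 shows what falls under that rule: "We will estimate Z score of the proximal segments of LMCA, LAD, and RCA at baseline, Day 5, 6-8 weeks, and 6 month". CAL at 6 months is listed there separately.

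The Statistical analysis text that follows the appendices says: "The primary outcome evaluation and safety evaluation are carried out on the intention-to-treat (ITT) population". It names no population for Z scores or 6-month CAL, so section 3.11 is the only rule for them. The available text does not define the PP population and does not explain why these outcomes differ from the other secondary outcomes.

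**The concern.** Section 2.2 states the secondary objectives as comparisons between the arms. Section 3.11 gives P < 0.05 as its only criterion, and the 10-point margin in section 3.6 is set for the primary endpoint. For a test of difference, the protection comes from keeping children in the groups to which they were randomised. A PP set conditions on what happens afterwards.

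The plan's own rules make selection plausible:

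- Section 3.9: families and investigators know the assigned arm.
- Section 3.2, withdrawal criteria: children can leave because of an allergic reaction to study treatment, an adverse event that leads to stopping it, or the investigator's judgement. Section 3.3 gives high-dose aspirin to the standard arm only, so aspirin-related exits may differ by arm.
- Section 3.3, prohibited treatment: steroids and biologics are barred during study treatment unless the child has withdrawn. Exit may therefore follow a worse illness course.

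If the children outside PP differ in coronary risk between arms, or differ in number at a raised risk, a PP-only result can hide a coronary difference or create one. No as-randomised result would be there to show it.

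The rule also divides data from the same visit. Sections 3.4 and 3.5 schedule laboratory tests and echocardiography together at Day 5 and 6-8 weeks. A child outside PP would count for CRP at that visit but not for the coronary Z score.

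**Working it through.** **Inputs from the documents**

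- Synopsis: "A total of 278 patients will be recruited to achieve 250 per-protocol (PP) patients". So 278 - 250 = 28 children, and 28/278 = 10.1%, are expected outside PP.
- Section 3.6: "The estimated proportions of CAL are 17% after IVIG and high-dose aspirin combination treatment and 15.4% after IVIG alone treatment". The CAL-free rates are 0.83 (standard) and 0.846 (test), the margin 0.10, alpha 0.05 and beta 0.2, with 125 per group, or 139 after a 10% dropout allowance.

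**Reproducing the plan's figure**

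n per group = (z₁₋α + z₁₋β)² × [p_S(1 - p_S) + p_T(1 - p_T)] / (margin + p_T - p_S)²

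- With one-sided alpha 0.05: (1.645 + 0.842)² × (0.1411 + 0.1303) / 0.116² = 124.7, rounded up to 125.
- Dropout: 125/0.9 = 138.9, rounded up to 139 per group, 278 in total. The plan's figures reproduce.

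**Precision**

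95% CI half-width = 1.96 × √(0.2714/n).

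- n = 125 per arm: 9.1 points.
- n = 139 per arm: 8.7 points.

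The gain in precision is small even if every child is scanned. Selection is the issue.

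**Illustration A: unequal numbers excluded**

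Assumptions, none of them in the documents: 6-month CAL is 10% in retained children of both arms and r in excluded children; all 28 excluded children have a 6-month scan; 139 are randomised per arm, of whom e are excluded.

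As-randomised rate in an arm = [(139 - e) × 0.10 + e × r]/139. PP shows 10% in both arms, a difference of zero. The as-randomised difference is (e_T - e_S) × (r - 0.10)/139.

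| Exclusions, test/standard | r = 0.20 | r = 0.30 | r = 0.40 |
|---|---|---|---|
| 14/14 | 0 | 0 | 0 |
| 19/9 | 10 × 0.10/139 = 0.7 points | 1.4 | 2.2 |
| 21/7 | 14 × 0.10/139 = 1.0 points | 2.0 | 3.0 |

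**Illustration B: equal numbers, unequal risk**

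Assumptions: true CAL is 17% in both arms and 14 of 139 are excluded in each. Exclusions in one arm carry risk r; those in the other carry the average 17%, so that arm's PP rate stays at 17%. The first arm's PP rate is (0.17 × 139 - 14r)/125.

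| r | PP rate | Spurious difference |
|---|---|---|
| 0.17 | 17.0% | 0 |
| 0.30 | 15.5% | 1.5 points |
| 0.40 | 14.4% | 2.6 points |
| 0.50 | 13.3% | 3.7 points |
| 0.60 | 12.2% | 4.8 points |

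Equal numbers are therefore not enough for safety; the risks must match too. No corresponding figure can be given for Z scores, because the documents supply no mean or spread for them.

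**The case against.** The strongest defence is that PP has a recognised role in a non-inferiority trial, and that 6-month CAL is the primary variable at a later visit. Section 3.11 puts both coronary outcomes in the same sentence and on the same set as the primary endpoint. Matching them is coherent, even though the plan does not say that this is the reason. It justifies keeping a PP analysis. It does not justify PP alone for outcomes that have no margin and are tested for a difference.

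The second objection is that the illustrated bias is small and rests on assumed risks and splits. That is correct: every illustrated value is below the 9-point half-width.

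Three stronger readings are tempting and are not supported:

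- A reader might infer that 28 scanned children will be discarded. Section 3.6 describes the 10% as dropout, and some withdrawn children may have no later scan. PP is not defined in the available text, so the number of measured children left out is unknown.
- A reader might infer that ITT would restore all 278 children. An analysis of children with a scan at the visit is an available-case analysis. It cannot recover a child who was never scanned, and selection through missing scans remains.
- A reader might infer that the fall in CAL from 6-8 weeks to 6 months will be distorted by a change of denominator. Under section 3.11 both time points are on PP. The distortion arises only if the primary outcome is taken on ITT, as the Statistical analysis text has it. It belongs to that separate contradiction and is not counted here.

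**Conclusion.** The point holds as a recommended improvement to two secondary outcomes. The plan provides no as-randomised comparison of coronary Z scores or 6-month CAL, although it uses ITT for the remaining secondary outcomes and its exit routes can depend on arm or illness course.

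The direction and amount of bias cannot be fixed from the documents. Under the stated assumptions, unequal exclusions hide 0.7-3.0 points of CAL, and equal numbers at unequal risk create 1.5-4.8 points. Exclusions alike in number and risk give about zero. Treating all 28 children as scanned sets the most that the change could recover within the plan's allowance. The planned sample size is not affected.

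**What to change.** In section 3.11:

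1. Analyse Z scores (at each scheduled visit) and 6-month CAL in every randomised child with an echocardiogram at that visit, in the assigned arm, whether or not the child deviated from or stopped study treatment.
2. Keep the PP analysis of both outcomes as supportive, and state which children the PP set excludes.
3. Report by arm how many randomised children have no echocardiogram at each visit. Add a simple sensitivity analysis for them, for example varying the assumed CAL risk in unscanned children separately in each arm.
4. Present 6-8-week and 6-month CAL side by side on the same population, whichever way the primary population is settled.

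The cost is a revised sentence or two and one extra set of tables from data already collected. The statistical downside is that deviations dilute the treatment contrast in the as-randomised result, which is why PP stays beside it.
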